#### Secondary outcome measures are the following

Stroke Impact Scale (SIS) version 3.0, other domains

The other 7 domains of the SIS 3.0 will be assessed as secondary outcome measures at baseline and 6, 12, 18 and 24 weeks after randomization

#### Motricity Index (MI)

The MI is a valid and reliable measure[39] and will be used to determine the strength of the upper (MI arm) and lower paretic limb (MI leg). Scores range from 0 (no activity) to 33 (maximum muscle force) for each dimension. The test has proved highly reliable and valid[39]. The MI will be assessed at baseline and 12 and 24 weeks post randomization.

#### Functional Ambulation Categories (FAC)

Walking ability will be determined using the FAC. It includes six categories with scores ranging from 0 to 5, viz. from unable to walk to independently walking without physical assistance[26,40], though only patients with FAC 3 or higher will be recruited for the FIT-stroke trial. The test will be applied at baseline and 12 and 24 weeks post randomization.

#### Six-minute walking test

The effects of functional fitness training on gait performance and endurance will be assessed by the 6-minute walking test (6-MWT)[41]. The test will be applied at baseline and 12 and 24 weeks post randomization.

#### Five-metre timed walk

Gait speed will be measured by the 5 meter comfortable walking speed test. Gait speed is responsive to change and closely related to walking performance in hemiplegic patients[40]. In order to reduce measurement error, the mean of three repeated walking speed measurements will be calculated[25]. Patients will rest for about one minute between each test. Using a digital stopwatch that records time within 0.01 second, timing will be manually started at the 'go' instruction and stopped when the subject crosses the 5 meter mark. The test will be applied at baseline and 12 and 24 weeks post randomization.

#### Timed balance test (TBT)

The TBT consists of 5 different components on an ordinal scale and involves timed balance (i.e., 60 seconds) on progressively diminishing support surfaces. The test has been shown to be reliable and closely related to walking performance[40,42]. The test will be used at baseline and 12 and 24 weeks post randomization.

#### Timed up and go test (TUG)

The TUG is a test of basic functional mobility. The participant is asked to rise from an armchair, walk 3 m as fast as possible, cross a line, turn, walk back and sit down again. The time taken to perform this task is recorded. The TUG has been shown to identify patients at increased risk of falls[43]. The test will be applied at baseline and 12 and 24 weeks post randomization.

#### Modified stairs test

The modified stairs test is an extended version of the Timed up and go test (TUG). The test includes the same tasks as the TUG, plus ascending and descending 5 steps[44]. Patients are timed to the nearest 0.01 s from the moment they are asked to rise from a chair which is placed 0.5 meters in front of the stairs, ascend 5 steps, turn and descend the 5 steps and sit down again in the chair as safely as possible. Patients rest for about one minute between each test. The test will be applied at baseline and 12 and 24 weeks post randomization.

#### Rivermead Mobility Index (RMI)

The RMI consists of 14 questions and one observation, covering aspects ranging from turning in bed to running[45]. Questions are simple and are scored dichotomously. The measure is reliable, valid and responsive [45-47]. The RMI will be applied at baseline, 12 and 24 weeks post randomization.

#### Nottingham Extended ADL (NEADL)

The NEADL scale[48] is based on a self-reported questionnaire on levels of activity actually performed. The NEADL consists of 22 items in 4 domains (mobility, kitchen, domestic, leisure). The NEADL is specifically designed for postal use with stroke patients, and has proved to be reliable and valid as an outcome measure in trials and observational studies. Each item is rated by one of four responses (able, able with difficulty, able with help, unable). The scale has been shown to have reasonable hierarchical (ordinal) properties in stroke patients. The NEADL will be assessed at baseline and 12 and 24 weeks post randomization.

All of the above tests, for both the experimental and control groups, will be implemented at the participants' own home by an independent observer who is blinded to treatment allocation.

#### Falls Efficacy Scale (FES)

The FES is an instrument to measure fear of falling, based on the operational definition of this fear as 'low perceived self-efficacy at avoiding falls during essential, nonhazardous activities of daily living'[49]. The FES will be assessed at baseline and 12 and 24 weeks post randomization.

#### Hospital Anxiety and Depression Scale (HADS)

The HADS is a simple measure to determine mood, emotional distress, anxiety, depression and emotional disorder. It is a brief, valid, reliable and widely used measure, known to produce meaningful results as a psychological screening tool. The HADS consists of 14 items (7 anxiety, 7 depression), each with a 4-point rating scale (0–3) and has proved to be responsive to change[50,51]. The HADS will be assessed at baseline and 12 and 24 weeks after randomization.

#### Fatigue Severity Scale (FSS)

The FSS will be used to assess the impact of fatigue. The FSS consists of 9 items, and scores for each item range from 1 to 7. The total FSS score is the mean of the 9 item scores[52]. In a reliability study with two independent observers and 18 stroke patients, FSS showed an intra-class correlation coefficient (ICC) of 0.82[53]. The FSS will be applied at baseline and 12 and 24 weeks post randomization.

#### Letter cancellation task

Inattention will be measured by the letter cancellation task[54] and will be scored positive when patients score three omissions or more on one side, compared to the other side.

#### Diaries

Finally, each patient will be asked to keep a cost diary, which will be used to assess medical consumption in both arms of the study. Patients will be asked to record their medical consumption (for example visits to a general practitioner, hospital visits, medication intake) each week. In addition, they will be asked to record their level of activities during the day (activity log) as well as special events (e.g. falls). This dairy will be kept daily for 12 weeks. After 12 weeks, the patients will be asked to continue recording weekly until 24 weeks after inclusion.

### Power analysis

A difference of 5 points (about 11%) on the 'mobility at home and in the community' domain of the SIS in favour of the experimental group will be regarded as clinically relevant[33], whereas the standard deviation for this population is estimated at a maximum of 14 points (28%) based on 287 mild and moderate SIS responses[55]. In addition, test-retest reliability (ICC) is known to be about 0.8[33], whereas the FIT-Stroke trial uses 4 repeated measurements in the first 24 weeks after randomization. Therefore, a minimum of 99 patients will be required for each arm of the trial. Expecting a dropout rate of 10%, we assume that a minimum of 220 stroke patients will be needed to achieve a sufficient statistical power of 80%.

### Data analysis

The present trial, with repeated measurements nested in each patient, will apply a random coefficients model (MLWIN, version 2.11) to evaluate differences in effect between the experimental and control intervention arms. Besides the type of intervention, the model will include significant factors such as covariates, which will be established by means of (univariate) regression analysis. It should be noted that Random Coefficient Analysis (RCA) is able to deal with (partially) or completely missing values and enables an 'intention-to-treat' analysis. Economic evaluation will be conducted from the main assumption underlying the present study, that the proposed fitness training programme, which allows stroke patients to train in groups of 8 to 10, will result in a better walking competency as well as improved (I)ADL and HRQoL, with net savings on resources (i.e., costs), compared to the control intervention. The balance between costs and effects will be estimated, in accordance with the Dutch guidelines for pharmaco-economic research, by means of multivariable probabilistic data analysis [56]. The cost diary will comprise detailed questions on items such as consultations with neurologists, family doctors, paramedics, home care and non-professional support, and the answers will be used in the costs evaluation. Provision of medication by pharmacies in the community will also be recorded to keep track of expenses related to drug use. The diary will also record low volumes of high-cost resources, such as re-admission to hospitals and rehabilitation centres. Ultimately, multiplication of resource use and unit costs, which will be determined in a separate cost study, will yield an estimate of patient-level cost. Subsequently, summation across individual patient records and averaging will yield an estimate of total costs per intervention arm. In addition, the impact of task-oriented CCT in terms of health-related quality of life will be determined using the EuroQol 5D (EQ-5D). The EQ-5D is a 5-item questionnaire that can be converted into a single value score (i.e., utility) for HRQoL, yielding an estimate of the quality-adjusted survival time (QALYs). This estimate will serve as the primary measure of effectiveness for the economic evaluation.

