A number of studies have shown that walking competency can be improved when practice is delivered in an intensive, and preferably task-oriented way [12-19]. For example, a meta-analysis of 13 RCTs (N = 501) showed that rehabilitation services in which the physical training is applied in a progressive and preferably task-oriented way are more effective than usual individual care, in terms of gait speed and walking distance[18]. Unfortunately, most stroke physiotherapists and occupational therapists are hampered in the implementation of intensive, task-oriented training by lack of time due to insufficient staff and inefficient use of human resources[20,21]. Group training, in which multiple patients practice meaningful tasks simultaneously, may be an effective method to overcome this problem. A recent meta-analysis showed that task-oriented circuit class training (CCT), in which training is organized as a circuit with a series of workstations, had positive effects in terms of gait speed, walking distance and the timed-get-up and go test, compared to usual care[19].

Task-oriented CCT generally seems to satisfy at least three key conditions for an effective and efficient physical training programme compared to usual face-to-face training. First, the use of different workstations in task-oriented CCT allows patients to practice intensively in a meaningful and progressive scheme suited to their individual needs. Second, task-oriented CCT might represent an efficient use of therapists' time while patients actively engage in task practice, compared to individual therapy. This makes circuit class training a potentially effective method which saves costs to the health care system by reducing staff-to-patient ratios. Third, task-oriented CCT involves group dynamics including peer support and social interaction[22].

Unfortunately, the literature offers only a few high-quality studies on the effectiveness of task-oriented CCT, whereas studies investigating its cost-effectiveness are still lacking[14,17,19]. The American Hearth Association recently emphasized the need for research to explore the health benefits and cost-effectiveness of structured exercise programmes to improve physical fitness in patients with stroke[8].

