### Intervention group

Patients assigned to the intervention group (two participants or more) will receive a 90-minute structured progressive task-oriented CCT programme twice a week over a twelve-week period (24 sessions). The programme includes 4 stages: (1) warming up (5 minutes), (2) circuit class training (60 minutes), (3) evaluation and a short break (10 minutes) and (4) group game (15 minutes). The training programme includes 8 different workstations, intended to improve meaningful tasks related to walking competency, such as balance control, stair walking, turning, transfers and speed walking. The eight workstations incorporated in the circuit are: (1) standing and reaching; (2) stair walking including transfer; (3) walking and picking up various objects from the ground; (4) kicking a ball; (5) stepping up and down; (6) walking course with obstacles; (7) transfers (lying to standing and sitting); and (8) speed walking. Graded progression will be achieved by (1) increasing the difficulty of the task; (2) adding weights; or (3) increasing the number of repetitions. No special (fitness) equipment is needed to perform the tasks. Each workstation will be done for 3 minutes, followed by 3 minutes of rest and 1 minute to change to the next workstation. The participants will complete the exercises in pairs, where one does the exercise while the 'partner' has a rest period and helps the other by keeping track of the number of repetitions and stimulates him/her to perform at their best. Time will be kept by the supervisors. The precise composition of the treatment package for each patient, in terms of appropriate selection of type of workstation, number of repetitions and intensity, will be determined at baseline, based on patients' profiles in terms of muscle strength, physical fitness and mobility status. All patients will keep an activity log in which they record the number of repetitions at each workstation during the sessions, which they will then use as feedback in the next session. The one-hour session of workstation training will be followed by a 15-minute group game, in which the whole group performs a game to improve walking competency. Games will vary across the sessions. Options include a game in which walking tasks are combined with a cognitive task, or a game consisting of fast walking and changing directions. Ball games can of course be used as well, as long as they serve to train walking performance. Incidents that occur during the training sessions (e.g. falls) will be reported by the supervisors to the independent investigator and registered in a falls diary. Patients who are allocated to the intervention group will receive no other physiotherapeutic treatment for the lower extremities.

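### CCT is given in interacting groups, but the planned model names no group level and the sample size has no design effect, so for any positive group ICC the standard error is too small and power falls short of 80%

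*Protocol article*

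**What the plan says.** **Delivery.** Among the conditions for an effective and efficient programme, the Background lists that "task-oriented CCT involves group dynamics including peer support and social interaction". Under Intervention group, "The participants will complete the exercises in pairs": the resting partner counts repetitions and encourages the other, and each session ends with a game for the whole group. The Definitions section has one or more therapists supervising a group. Control patients receive usual individual physiotherapy (Abstract; Control group).

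**Group size.** Three statements appear: 4 to 6 (Abstract), at least 2 (Definitions; Intervention group) and 8 to 10 (economic part of Data analysis).

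**Analysis.** The Data analysis section states: "The present trial, with repeated measurements nested in each patient, will apply a random coefficients model". Covariates are to be picked by univariate regression. Training group, supervisor and centre are not named as levels. Centre is the stratification factor (Procedure).

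**Sample size.** The Power analysis takes a difference of 5 points and an SD of at most 14 on SIS mobility, adds that "test-retest reliability (ICC) is known to be about 0.8" and that "the FIT-Stroke trial uses 4 repeated measurements in the first 24 weeks after randomization", and concludes: "Therefore, a minimum of 99 patients will be required for each arm of the trial". With 10% dropout this becomes 220.

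**The concern.** Patients who train together share a supervisor, a working partner and a group atmosphere. If the named mechanism operates, their outcomes are correlated, and that correlation adds to the variance of the CCT arm's mean. A model that recognises only visits within patients treats all CCT patients as independent. It then reports a standard error that is too small, and the test rejects too often under the null.

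The sample size has the same gap. Its only ICC is test-retest reliability within a patient, which says nothing about correlation between patients.

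The comparison is meant to show that CCT is better than individual therapy (Background) or at least as good (Discussion). A standard error that is too small favours a false claim of superiority and makes an interval quoted in support of similarity too narrow.

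**Working it through.** **Inputs from the Power analysis:** difference 5, SD 14, within-patient ICC 0.8, 4 measurements, 99 per arm, 10% dropout, 80% power. Alpha is not stated; two-sided 0.05 is assumed. The group ICC (ρ, on the scale of the patient's mean over visits) is not in the article; 0.01 to 0.10 is assumed. Group size m is taken from the article's own statements.

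**Step 1: reproduce the stated figure.** One measurement per patient, independent patients:

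n = 2 × (1.960 + 0.842)² × 14² / 5² = 123.07 per arm.

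Multiplying by 0.8 gives 98.46, so 99; and 2 × 99 / 0.90 = 220. Both stated figures are matched, with patients treated as independent. The implied standard error is 14 × √(2 × 0.8 / 99) = 1.780, and power is Φ(5/1.780 − 1.960) = 80.2%. This is the base used below.

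**Step 2: add clustering in the CCT arm only.**

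- Design effect in the CCT arm: DE = 1 + (m − 1)ρ
- Variance ratio of the treatment difference: R = (1 + DE) / 2
- Type I error if the model ignores the group: 2 × [1 − Φ(1.960/√R)]
- Power of a valid 5% test at 99 per arm: Φ(5/(1.780√R) − 1.960)
- n per arm that would restore 80%: 98.46 × R, rounded up

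Example, m = 6 and ρ = 0.05: DE = 1.25 and R = 1.125. The true standard error is 1.780 × 1.061 = 1.888, type I error 6.5%, power 75.4%, n = 111 per arm.

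| m | ρ | R | Type I error, group ignored | Power, group respected | n per arm for 80% |
|---|---|---|---|---|---|
| 4 | 0.01 | 1.015 | 5.2% | 79.6% | 100 |
| 6 | 0.01 | 1.025 | 5.3% | 79.2% | 101 |
| 4 | 0.05 | 1.075 | 5.9% | 77.3% | 106 |
| 6 | 0.05 | 1.125 | 6.5% | 75.4% | 111 |
| 4 | 0.10 | 1.150 | 6.8% | 74.5% | 114 |
| 6 | 0.10 | 1.250 | 8.0% | 71.0% | 124 |
| 8 | 0.05 | 1.175 | 7.1% | 73.6% | 116 |
| 10 | 0.05 | 1.225 | 7.7% | 71.8% | 121 |
| 8 | 0.10 | 1.350 | 9.2% | 67.6% | 133 |
| 10 | 0.10 | 1.450 | 10.4% | 64.5% | 143 |

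The type I and power columns describe alternative analyses: the first is what happens if the group is left out, the second is what remains once it is modelled. The rows for 8 and 10 are an upper extreme, because that group size appears only in the economic rationale and conflicts with 4 to 6.

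**Step 3: sensitivity of the base.** The usual variance factor for the mean of 4 measurements with ICC 0.8 is (1 + 3 × 0.8)/4 = 0.85, not 0.8. It gives 105 per arm, and power at 99 of 77.8% with no clustering at all. That loss of 2.4 points is a separate matter and is not counted here. The type I column does not depend on this choice.

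**The case against.** **The article is condensed, and random-effects detail often sits in a SAP.** This stands in part. A reader might infer that the model has two levels and nothing more. The text does not say so: it does not rule out a group or centre term, and it leaves covariates open. What can be said is that it names no group level. The sample size is firmer ground, since 99 per arm and 80% power are stated outright and contain no allowance for correlation between patients.

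**The group ICC is assumed and may be small.** This stands. Workstations, repetitions and intensity are set for each patient at baseline, which may limit shared variation. At 0.01 the power loss is under 2 points for every group size considered.

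**Larger groups are weakly grounded.** This stands. About 110 CCT patients over nine centres is about 12 per centre for the whole trial, so a concurrent trial group of 8 to 10 would take up most of a centre's CCT patients. A reader might go further and treat all CCT patients at a centre as one cluster under a single team. The article does not support that: about 60 therapists were trained, six or seven per centre, and nothing says that one team treats everyone.

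**Clustering may not be confined to CCT.** This stands. Controls at the same centres may share physiotherapists. Any such correlation would add to the variance, so leaving it out does not rescue the plan.

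**Groups may be rolling.** Patients enter individually at discharge, so membership may overlap. The simple design effect is then an approximation.

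**Centre adjustment might absorb the problem.** Only in part: it would remove variation between centres but not variation between groups or supervisors within a centre.

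**Conclusion.** The point holds. The article describes a group-delivered treatment with interaction as part of its mechanism, names an analysis without a group level, and sizes the trial as if patients were independent. The direction is certain for any positive group ICC.

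The size is conditional on the assumed ICC, fixed group sizes, equal allocation, two-sided 0.05 and independent controls. With groups of 4 to 6, the range is from negligible (ICC 0.01: type I error 5.2% to 5.3%, power above 79%) to material (ICC 0.05: 5.9% to 6.5% and 77% to 75%; ICC 0.10: 6.8% to 8.0% and 75% to 71%). Type I error of about 10% and power of about 65% is an outer bound that needs both groups of 10 and an ICC of 0.10. The documents do not establish that the trial is severely underpowered; they show that the stated 80% is the value under independence and has no margin for clustering.

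**What to change.** 1. In the primary model, add a random effect for training group in the CCT arm, or for supervisor team or cohort within centre if membership rolls. Include centre as a fixed effect and use small-sample degrees of freedom.
2. Record training group and supervisor in the session logs from the first patient, since membership may not be recoverable later. Record the treating therapist for controls, so that clustering in that arm can be examined in a sensitivity analysis.
3. Reconcile the group sizes in the Abstract, the Definitions and Intervention group sections, and the Data analysis section.
4. Restate the power of 220 patients with an explicit group size and ICC range, for example 0.01 to 0.10 as above.

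The cost is some analysis wording, identifiers in the logs, slightly wider confidence intervals and a lower stated power. No extra patients are required, provided the lower power is stated openly; the last column of the table shows what restoring 80% would take.

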### Setting

The study will be conducted in nine rehabilitation centres in The Netherlands ('De Hoogstraat', Utrecht; 'Heliomare', Wijk aan Zee; 'Rijnlands Revalidatiecentrum', Leiden; 'Sophia Revalidatie', Den Haag; 'Stichting Revalidatie Breda', Breda; 'Via Reva/Kastanjehof', Apeldoorn; 'Roessingh', Enschede; 'De Trappenberg', Huizen and 'Vogellanden', Zwolle). All patients will complete an inpatient rehabilitation period and will be included when they start their outpatient rehabilitation period.

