### Procedure

Patients will be stratified by rehabilitation centre and subsequently randomized to task-oriented CCT or to individual face-to-face physiotherapy, using an 'online' minimization procedure[27]. The intervention period will be 12 weeks and measurements will be taken at baseline, 6, 12, 18 and 24 weeks. All outcomes measured at baseline, 12 and 24 weeks will be assessed in face-to-face meetings by an independent researcher, blinded for treatment allocation, whereas at 6 and 18 weeks, a restricted set from the test battery will be assessed by semi-structured telephone interviews (Figure 1).

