#### Stroke Impact Scale (SIS) version 3, Mobility domain

The SIS is a self-reported, stroke-specific measure that includes 59 items and assesses 8 domains related to activities and participation[32]. The mobility domain of the SIS includes 9 questions about patients' perceived competency to keep their balance, to transfer, to walk indoors and climb stairs, to get in and out of a car and to move in their own community. Each item is scored from 'not difficult at all' to 'cannot do it at all' on a 5-point scale. A difference of 10 points on the 'mobility at home and in the community' domain of the SIS is regarded as clinically relevant[33]. SIS has shown excellent clinimetric properties in terms of concurrent and construct validity, test-retest reliability and responsiveness[33,34]. Proxies can also provide valid information on SIS outcome[34]. The SIS has recently been translated into Dutch and the Dutch version showed similar clinimetric properties when re-tested in 27 stroke patients[35]. The SIS will be applied at baseline and 6, 12, 18 and 24 weeks after randomization.

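### The primary model's covariates are chosen by a univariate significance screen, so the model is not fixed in advance and neither baseline score nor centre is guaranteed a place

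*Protocol article*

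**What the plan says.** The Data analysis section applies a random coefficients model to repeated measurements nested in patients. The intervention is the only term it guarantees. On everything else it says that "the model will include significant factors such as covariates, which will be established by means of (univariate) regression analysis". It names no term that enters regardless of the screen, and the only nesting it mentions is measurements within patients.

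Two variables have an obvious claim to a place in the model:

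- **Centre.** Under Procedure, "Patients will be stratified by rehabilitation centre and subsequently randomized to task-oriented CCT or to individual face-to-face physiotherapy", "using an 'online' minimization procedure". Under Setting, "The study will be conducted in nine rehabilitation centres in The Netherlands". The Design section confirms that allocation takes place within each centre.
- **Baseline score.** In the section on the SIS mobility domain, "The SIS will be applied at baseline and 6, 12, 18 and 24 weeks after randomization". The Power analysis section counts four repeated measurements after randomisation, so baseline is apparently not one of the modelled outcomes.

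Nothing in the article puts either variable in the primary model.

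**The concern.** This is a stated rule, not a detail left open. If the covariates are those that prove significant when the outcome is regressed on each factor, the confirmatory model cannot be known until outcomes are in. The article collects many baseline variables and four follow-up visits, so more than one adjusted model could be reached under this rule, each with its own treatment estimate.

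The screen also asks the wrong question of a design factor. Centre belongs in the model because allocation was stratified on it, whatever its p-value in this sample. The baseline value of the outcome belongs there because it can be expected to predict follow-up. At stake are a primary estimate fixed before outcomes are seen and an analysis that matches the randomisation.

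**Working it through.** **Inputs from the Power analysis section.** Difference 5 points ("A difference of 5 points (about 11%) on the 'mobility at home and in the community' domain of the SIS"), SD 14, ICC 0.8, four follow-up measurements, 99 per arm, 10% dropout, 220 in total. Number of centres: nine (Setting).

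**Assumed, because the article does not give them.** A 5% cut-off for the screen, two-sided 5% testing, between-centre ICC 0.01 to 0.10, equal centres of 198/9 = 22 patients, and a range of baseline-outcome correlations.

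**Step 1: the plan's own figure.** 2 × (14 × (1.960 + 0.842)/5)² = 123.07 per arm; × 0.8 = 98.5, so 99; 2 × 99/0.9 = 220. Both stated figures reproduce this way. They serve here only to set the analysed sample at 198.

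**Step 2: how often centre survives the screen, and what omitting it does.** The one-way F test has 8 and 189 df and a 5% critical value of 1.99.

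- P(kept) = P(F(8,189) > 1.99/(1 + 22 × ICC/(1 − ICC))).
- With allocation balanced within centre, a model without centre charges between-centre variance to the error term. Its SE is therefore too large by about 1/√(1 − ICC).
- Type I error is then 2 × (1 − Φ(1.96/√(1 − ICC))).

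| ICC | Centre kept | SE too large by | Type I error if omitted |
|---|---|---|---|
| 0.01 | 12% | 0.5% | 4.9% |
| 0.02 | 21% | 1.0% | 4.8% |
| 0.05 | 50% | 2.6% | 4.4% |
| 0.10 | 80% | 5.4% | 3.9% |

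The screen is likeliest to drop centre where dropping it matters least.

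**Step 3: how often baseline survives.** By Fisher's z with n = 198, P(kept) ≈ Φ(atanh(r) × √195 − 1.96).

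- r = 0.15: 0.151 × 13.96 = 2.11, so about 56%.
- r = 0.3: 0.310 × 13.96 = 4.32, so about 99%.
- r = 0.5: 0.549 × 13.96 = 7.67, so above 99.99%.

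**Step 4: never adjusting against always adjusting.** For the mean of four visits, unadjusted SE = 14 × √(((1 + 3r)/4) × 2/99) and baseline-adjusted SE = 14 × √(((1 + 3r)/4 − r²) × 2/99).

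- r = 0.8: 1.83 falls to 0.91.
- r = 0.5: 1.57 falls to 1.22.

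Step 3 shows that at these correlations the screen would keep baseline, so these differences are not what the rule is expected to cost.

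**Step 5: the rule as a whole, by simulation.** Settings: 198 patients, nine centres, SD 14, one summary outcome per patient, ten irrelevant candidate covariates, baseline correlation 0.15, 0.5 or 0.8, centre SD 2 or 4 points, 2000 runs per setting.

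| Result | Screened model | Model fixed with baseline and centre |
|---|---|---|
| Centre included, centre SD 2 | 18–22% | always |
| Centre included, centre SD 4 | 65–69% | always |
| Baseline included, r = 0.15 | 51–55% | always |
| Baseline included, r = 0.5 or 0.8 | 100% | always |
| Type I error | 4.5–5.4% | 4.5–5.5% |

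Power for 5 points differed by at most 1 percentage point between the two models. A centre SD of 2 corresponds to an ICC of 4/(4 + 196) = 0.02, for which Step 2 gives 21%, in line with the simulated 18–22%.

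**The case against.** The strongest reply is that applying the rule mechanically does no visible damage. That stands: type I error held at its nominal level and power was nearly the same as with the fixed model.

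Three stronger readings are tempting, and the documents do not support them.

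- **The rule could double the standard error.** The drop from 1.83 to 0.91 compares never adjusting with always adjusting. The plan says neither, and a screen would keep a baseline score that predictive.
- **Omitting centre makes the test too liberal.** With allocation balanced within centre, the error runs the other way and is small.
- **The QALY analysis has the same fault.** The quoted sentence concerns the random coefficients model. The article gives the economic evaluation its own method, a multivariable probabilistic analysis.

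It can also be said that the text names no dependent variable for the univariate regressions, and that a random coefficients model could carry centre as a level or baseline as an occasion. Both are true. Regression of the outcome on each factor remains the natural reading, and nothing in the article says that centre or baseline enters by another route.

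Finally, a candidate list and cut-off are commonly left to an analysis plan, and their absence is not held against the article. The fault lies in the screen that the article does state. An analysis plan that fixed the covariates in advance would depart from it.

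**Conclusion.** The point holds in limited form. The stated screen means that the adjusted primary model is not fixed before outcomes are seen, and that the analysis is not guaranteed to match the centre-stratified allocation or to use the baseline score. This rests on reading the univariate regressions as regressions of the outcome on each factor.

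The size is modest. Centre would be absent from about 20% to 88% of trials over the assumed ICC range (the complement of 80% to 12%), with a slightly conservative test when it is absent. Baseline is at real risk only at weak correlations, where little precision is lost. A reader might infer an inflated false-positive rate or a large loss of power; the calculations show neither under mechanical use. The case for change is prespecification and agreement with the design. It should be corrected, but it does not threaten the trial's validity.

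**What to change.** Remove the univariate significance screen from the primary analysis. State in advance that the model contains intervention, visit, the baseline value of the outcome, rehabilitation centre (as a fixed or a random effect) and any other factor used in the minimisation. A model with screened covariates may be reported, but only as a labelled sensitivity analysis.

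The cost is one sentence in the Data analysis section and no new data. Centre uses at most eight degrees of freedom with about 198 patients analysed. If a screen would nearly always have kept the baseline score, naming it in advance loses nothing.
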